#### Exclusion criteria

Anyone not meeting the above criteria by definition will be excluded from the study. In addition, the following exclusion criteria will apply:

1. Major psychiatric illness. The treatment for a major psychiatric illness may interfere with the program.

2. Active alcohol or drug dependency. Any alcohol or drug dependency may interfere with the program.

3. Scheduled for major surgery in the next 3 months. Any scheduled surgery within the next 3 months will interfere with the program schedule.

4. Participation in a pharmacological study or psychological intervention study within the last 6 months or intention to participate in a pharmacological study during the duration of this study. Both will interfere with the program.

5. Have recently (within the last 3 months) been prescribed antidepressants. Any change of antidepressant in the last 3 months may interfere with the program.

6. With exacerbated symptoms (acute phase). Having exacerbated symptoms will make it very difficult for participants to attend the two hourly sessions or to commit to the home practice. This could cause extra unwanted stress for the patient.

#### Randomisation

Randomisation will be performed using a dedicated software solution after participants have given written consent and baseline data have been collected. Group allocation will be to ‘MBCT group’ or ‘wait-list control group’ in a 1:1 ratio. To ensure similarity between the groups, randomisation will take account of gender and type of disease. The randomisation will be carried out by an independent statistician.

#### Minimising bias

Participants will self-complete all the questionnaires. Data entry will be done by the lead researcher and independently checked by a second person. Data analysis will be done by two researchers independently and differences will be rectified by a third person.

#### MBCT intervention

The MBCT program used in this study will follow the manual developed by Segal et al. [31]. In brief, the manual proposes the following format for the eight group sessions:

•Welcome and introduction to the session theme

•A short opening meditation

•A discussion of at-home practice

•An introduction and practice of new exercises

•A group reflection/discussion

•A review of the next weeks’ at-home practice

•A closing sitting meditation

A sample list of activities for session 1 is presented below. The manual also suggests for an additional full day of mindful practice to take place between weeks 6 and 7 (usually on a weekend). In the full day of practice participants will go through all the learned meditations one after another in silence, with the group reflection and discussion taking place at the end of the practice day. An example schedule for a day of mindful practice is presented below. Due to resource constraint, in this study, the full day of practice will be offered to participants after they have completed the 8-week course.

### A sample list of activities for session 1

Theme: Awareness and automatic pilot

1. Establish the orientation of the class

2. Set ground rules regarding confidentiality and privacy

3. Ask participants to pair up and introduce themselves to each other than to the group as a whole, giving their first names and if they wish, saying what they hope to get out of the program

4. The raisin exercise

5. Feedback and discussion of the raisin exercise

6. Body scan practice-starting with short breath focus

7. Feedback and discussion of body scan

8. Home practice assignment:

• Body scan for 6 out of 7 days

• Mindfulness of a routine activity

• Distribute audio files: cd’s for those that not have email and session 1 participant hand-outs.

9. Discuss in pairs:

• Timing for home practice

• What obstacles may arise

• How to deal with them

10.  End the class with a short 2–3 minute focus on the breath.

### Example schedule for a day of mindful practice [35]

9.45-10.00 Arrival

10.00-10.05 Sit in silence

10.05-10.20 Welcome, introduction, ground rules

10.20-10.50 Siting meditation: Breath, body, sounds, thoughts and choiceless awareness

10.50-11.30 Mindful stretching

11.30-12.00 Body scan

12.00-12.05 Instruction for lunchtime: bringing focus on awareness of eating, tasting, chewing, swallowing, slowing down

12.05-13.05 Lunch followed by mindful walk

13.05-13.20 Sitting meditation

13.20-13.50 Walking meditation

13.50-14.20 Mountain meditation

14.20-14.40 Mindful stretching

14.40-15.00 Silent sit or extended breathing space

15.00-15.30 Feeding back experience of day in pairs

15.50-16.30 Large group discussion and close

The program will be delivered by two experienced MBCT practitioners that have been briefed on the key concerns and difficulties that IBD patients experience as well as the nature of the disease. An experienced practitioner will have completed an 8-week MBCT course and maintained a personal practice for at least 1 year. In addition they will have facilitated at least one 8-week MBCT program.

Participants will be encouraged to do daily home practice for the duration of the program and keep a home practice diary. Participants will be provided with guided practice CDs and hand-outs with a written summary for each session and instruction for home practice. Each weekly session will be approximately 120 minutes and will be audio recorded.

#### Wait-list control

The control group will continue to receive their standard care and in addition will receive a leaflet entitled ‘Staying well with IBD’. The leaflet is readily available to download from the Crohn’s and Colitis UK website, but participants in the study will receive a printed copy [42]. After 6 months follow-up data are collected; the wait-list group will have an opportunity to attend a MBCT program if they wish.

#### Data collection

A screening and recruitment log will be completed by a researcher to document all patients considered for the study and subsequently included or excluded at each stage of the recruitment process with reasons given. This log will include information such as date when information was given about the study, and date of recruitment and randomisation. The data will inform the estimate for recruitment rates for a full trial and address aims 1 and 4. A full consort diagram of subject flow is presented in Figure 1.

**Figure 1 F1:**
[figure not shown]
Consort diagram describing flow of patients through study.

At baseline, demographic information including age, gender, education, income and marital status will be recorded, to allow the success of randomisation to be assessed [43].

The MBCT practitioners will complete an attendance log to document the number of practice sessions attended by each participant. This log will inform the estimated attrition rates for a full trial and will address aim 3.

Semi-structured interviews with the practitioners delivering the MBCT intervention will be conducted to find out if any changes to the manual should be done to accommodate the needs of this patient group. This will address aim 2.

#### Outcomes and assessments

The outcomes for this study are consistent with relevant published studies assessing the use of mindfulness-based program in populations with chronic health problems [44] as well as with studies investigating the effects of non-pharmacological programs on QoL in IBD patients [35,36,45]. They include assessment of disease specific QoL, mood, mindful awareness, disease activity and demographics. All assessment tools used in the trial are validated and reliable. All outcomes will be assessed at baseline, post treatment and 6 months.

#### Proposed primary outcome

##### Quality of life

All participants will be required to complete the disease specific IBD quality of life (IBDQoL) questionnaire consisting of 32 questions. The questionnaire has four domains, including bowel symptoms, systemic symptoms, emotional factors and social factors. Within the questionnaire, participants will rate their symptom experience over the previous 2 weeks. Low scores indicate more severe disease activity and/or higher emotional and social dysfunction. A relatively good correlation between the IBDQoL and a widely used measure of disease activity, the Crohn’s Disease Activity Index is reported (*r* = -0.67; *P* <0.001) [46,47].

#### Proposed secondary outcomes

##### Anxiety

Anxiety will be measured by the State and Trait Anxiety Inventory (STAI) Y1 and Y2 form, consisting of 40 questions on a self-report basis. The inventory measures two types of anxiety: anxiety related to an event and anxiety level as a personal characteristic. Higher scores are positively correlated with higher levels of anxiety [48]. This tool is widely used to measure anxiety and regarded as highly reliable [13].

##### Depression

Low mood and depression symptoms will be measured with the Beck’s depression inventory (BDI-II), consisting of 21 group of statements referring to the last 2 weeks. Each answer is being scored on a scale value of 0 to 3. Higher total scores indicate more severe depressive symptoms. Previous studies indicate the internal consistency of the BDI-II is high [49,50].

##### Disease activity

Disease activity will be measured with the eight-item questionnaire Crohn’s Disease Activity Index (CDAI) for Crohn’s patients [51,52] and six-item questionnaire Simple Clinical Colitis Activity Index (SCCAI) for ulcerative colitis patients [53]. Both tools are widely used to measure disease activity with IBD patients.

##### Mindful attention

Mindful attention will be measured with the 15-item scale Mindful Attention Awareness Scale (MAAS). This scale consists of collection of statements about everyday experiences graded by participants, using a scale of 1 to 6 which indicates how often each experience occurs. Higher scores reflect higher levels of dispositional mindfulness. The validation of this tool has been examined in a series of studies indicating strong psychometric properties and validity [54,55].

### Phase 2 - Process evaluation

To address aim 5 and examine the implementation and receipt of the intervention and trial procedures, a detailed process evaluation will be undertaken. This evaluation process will assess the acceptability of recruitment, randomisation and consent procedure for patients, acceptability and feasibility of collecting reliable and valid data on primary and secondary outcomes, fidelity of protocol, acceptability of length of intervention for patients, appropriateness/suitability of the intervention used, barriers to attendance, expectations about intervention and perceived impact on QoL.

Observations of MBCT training sessions will be undertaken by audio recording of all sessions to assess if specific components of the protocol are delivered and to use the qualitative data to assess the appropriateness of the intervention used. These data will address aim 5c.

All participants will be asked to self-complete a postal survey asking their views on research procedures such as consent and randomisation procedures and reliability of questionnaires. The MBCT group will answer further questions on expectations, acceptability, appropriateness and perceived impact of the intervention as well as the length of the program. These data will address aims 5a, 5e, 5f, 5g and 5h.

A post-intervention focus group will be facilitated to further explore the participants’ views and experiences of the MBCT program and trial procedures, using the themes from the survey. The focus groups will be audio recorded. A list of topic guides for the focus group is presented below.

### List of topic guides for the focus groups

  Expectations

1. Did you have any expectations regarding the self-help program?

2. If yes, what were they?

3. Were your expectations met/ unmet in any way? And How?

Length and difficulty of program

4. Was the length of eight weeks for the program acceptable?

5. Did you find the program difficult to follow?

6. Please tell us which specific parts of the program you found difficult to follow.

Potential benefits

7. Do you think this program has brought any benefit to you?

8. Please tell us how you think the program benefited you.

9. Do you think you will continue to use some of the techniques you learned in the program?

Recruitment and randomisation

10. Do you think the process of recruitment was acceptable?

11. Do you think the patient information sheet was easy to understand?

12. Any suggestions to make it clearer to understand

13. Did you feel comfortable with the process of consent and randomisation?

Questionnaires

14. Was filling the questionnaires at the start and at the end of the eight weeks too much of a burden?

15. Can you please tell us what difficulties you came across with the questionnaires and perhaps any suggestions of how to overcome those difficulties

Barriers to attending

16. Were there any barriers to attending the program?

17. Can you please tell us what you think were barriers to attendance?

What did you enjoy?

18. Did you enjoy the program?

19. Which parts did you most enjoy?

Availability of MBCT program

20. Do you think this program should be made available to IBD patients through NHS?

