### Aims and objectives

The overall aim of this study is to pilot the MBCT program with IBD patients in a RCT and examine the feasibility of running a large RCT testing the above hypothesis.

The specific objectives of the pilot are:

1. To determine the feasibility of conducting a large-scale RCT of group MBCT for improvement of IBD QoL.

2. To adapt the intervention manual devised by Segal et al. [31], outlining how to carry out an MBCT program for IBD patients.

3. To use data arising from differences between MBCT and control arm to inform a power calculation for sample size of a definitive RCT.

4. Estimate trial eligibility, recruitment (percentage of IBD patients who consent to the trial) and completion/retention rates (percentage of participants completing the trial).

5. To embed a process evaluation within the pilot trial to assess the acceptability of the intervention and trial procedures for IBD patients, such as:

a. Acceptability of recruitment, randomisation and consent procedure

b. Acceptability and feasibility of collecting reliable and valid data on primary and secondary outcomes (including follow-up at 6 months)

c. Fidelity of intervention.

d. Acceptability of length of intervention

e. Appropriateness/suitability of the intervention used

f. Barriers to attendance

g. Expectations about intervention

h. Perceived impact on QoL

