## Methods and design

### Design

This exploratory trial is designed in two phases. Phase 1 is a two-arm pilot RCT (MBCT treatment *vs*. wait-list control group) with three assessments (baseline, post treatment and 6 months). Phase 1 will assess eligibility, uptake, drop-out rates and sample size calculation as well as adaptation and adherence to MBCT manual. This design is consistent with similar studies where a non-pharmacological intervention is investigated in IBD population [32-38].

Phase 2 is a process evaluation assessing the feasibility and acceptability of the intervention, primary and secondary outcomes and trial procedures as well as barriers to attendance and perceived benefits to patients. This design is in line with the Medical Research Council (MRC) framework for the development and evaluation of complex interventions to ensure that both the intervention and trial procedures are optimised and can be incorporated into routine clinical practice [39].

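### The focus-group guide asks about the program's effects in the positive direction only, and none of its 20 items asks about worsening or unwanted effects

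*Protocol article*

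**What the plan says.** Under Aims and objectives, the last of the process-evaluation topics (objective 5h) is "Perceived impact on QoL", which favours neither direction. The Design section describes the same evaluation as covering "barriers to attendance and perceived benefits to patients".

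The List of topic guides for the focus groups has 20 items under eight headings. The questions on effect and experience stand under Potential benefits (items 7 to 9) and What did you enjoy? (items 18 and 19):

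- Item 7: "Do you think this program has brought any benefit to you"
- Item 8: "Please tell us how you think the program benefited you"
- Item 9 asks whether participants expect to go on using the techniques.
- Item 18 asks whether they enjoyed the program.
- Item 19: "Which parts did you most enjoy"

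The Process evaluation section gives the focus groups the job of exploring participants' views and experiences further, starting from themes raised in a postal survey. In that survey the MBCT group is asked about, among other things, the intervention's perceived impact. The survey's items are not printed.

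**The concern.** An objective that asks about impact needs an instrument through which impact of either sign can come out. Here the neutral objective becomes perceived benefits in the Design section and Potential benefits in the guide. A facilitator who follows the guide asks every group how the program helped, and never asks whether it did anything unwelcome.

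Prompted and volunteered answers are not comparable, least of all in an audio-recorded group. If few unwanted effects are reported, the reader cannot tell whether there were few or whether nobody was asked. The balance of the focus-group account of perceived impact, and its value for judging whether the intervention is suitable and for planning the definitive trial, are at stake.

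**Working it through.** No formula applies. The plan's own design figure, 40 randomised to leave 30 completers at 25% attrition, reproduces (30 / 0.75 = 40) and plays no part here. The check is a count of the printed items, followed by a comparison with the objective and the other data sources.

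**Step 1. Count by heading.**

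| Heading | Items | n | Room for a negative answer |
|---|---|---|---|
| Expectations | 1–3 | 3 | Yes, on unmet expectations (item 3) |
| Length and difficulty | 4–6 | 3 | Yes, on length and on following the program |
| Potential benefits | 7–9 | 3 | Only a bare no at items 7 and 9 |
| Recruitment and randomisation | 10–13 | 4 | Yes, on trial procedures |
| Questionnaires | 14–15 | 2 | Yes, on burden and difficulties |
| Barriers to attending | 16–17 | 2 | Yes, on attendance |
| What did you enjoy? | 18–19 | 2 | Only a bare no at item 18 |
| Availability | 20 | 1 | A no, on NHS provision |

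Total: 3 + 3 + 3 + 4 + 2 + 2 + 2 + 1 = 20. The benefit and enjoyment headings hold 3 + 2 = 5 items, and the other headings hold 20 − 5 = 15. Items asking about worsening, distress or unwanted effects: 0 of 20.

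**Step 2. Direction of the effect questions.** Items 7, 8, 18 and 19 ask for something positive. Items 7 and 18 can be answered no, but nothing follows up a no. Item 8 takes benefit as given; by contrast, item 2 is explicitly conditional on a yes to item 1. Item 19 asks for the best-liked parts and has no least-liked partner. Item 9 concerns continued use rather than effect.

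**Step 3. Against the objective.** Objective 5h covers improvement, no change and deterioration alike. The effect items prompt for the first, allow the second as a bare no, and do not ask about the third.

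**Step 4. Other sources.** IBDQoL, STAI, BDI-II and the disease activity indices are collected at baseline, post treatment and 6 months, and each can move in the unfavourable direction. A changed score does not say whether the participant attributes it to the practice, which component was upsetting, or whether it affected attendance. The survey's perceived-impact wording is neutral, but its items cannot be inspected.

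**The case against.** The strongest reply is that the guide is one instrument among several and is not uniformly favourable. Item 3 asks "Were your expectations met/ unmet in any way? And How", item 6 asks "Please tell us which specific parts of the program you found difficult to follow", and items 14 to 17 invite complaints about questionnaires and attendance. Unconditional follow-ups are also the guide's habit in the negative direction, as item 6 shows. The article assigns objective 5h to the survey, whose wording is neutral and whose themes feed the focus groups. The scales would show worsening of mood, anxiety or bowel symptoms, and practitioner interviews ask whether the manual needs changing.

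Much of this stands. A reader might infer that the guide asks only about benefit and enjoyment; it does not, since 15 of 20 items are on other topics. A reader might also infer that the pilot as a whole cannot see harm. The scales and the survey contradict that, and any adverse-event procedure may sit in the full protocol, which is not shown.

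The reply does not supply the missing question. The items that invite negative answers concern expectations, difficulty, questionnaires and attendance. Worsening would surface through item 3 only if a participant happened to think of it as an unmet expectation. The source meant to explore experience in depth still prompts in one direction.

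**Conclusion.** The point holds in a limited form and is minor. The guide's effect questions (items 7, 8, 18 and 19) run in the positive direction, no item of 20 asks about worsening or unwanted effects, and the focus-group findings would lean towards perceived benefit. The size of the lean cannot be estimated from the document. Recruitment, retention, sample size and the quantitative outcomes are unaffected. The conclusion assumes that the guide is used broadly as printed and that themes carried over from the survey do not already fill the gap.

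Three further inferences are tempting and are not supported:

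- That the plan names a harm and then fails to ask about it. Exclusion criterion 6 does say "This could cause extra unwanted stress for the patient", but of people in the acute phase, who are not enrolled; participants must be in remission.
- That participants are selected for raised anxiety or depression. No inclusion criterion requires either; the Background says only that rates are higher among IBD patients.
- That the objective on length of the intervention (5d) is compromised. Item 4 asks about length directly.

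**What to change.** In the topic guide:

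- Retitle Potential benefits as *Effects of the program*.
- Replace items 7 and 8 with a neutral pair, for example: *Did the program change how you feel or your symptoms, for better or worse?* and *Was anything unwanted or upsetting, and did it affect your attendance or home practice?*
- Add a counterpart to item 19 asking which parts were least enjoyed.

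In the MBCT group's postal survey, check whether the perceived-impact questions already allow answers in both directions; if not, word them the same way. The survey is self-completed, so it also reaches people who would not speak in a group. In the report, set unwanted effects beside perceived benefits.

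The cost is a minor amendment and a slightly longer guide or survey, with no extra visits or staff. The article gives recruitment as ongoing, so groups not yet held could use the revised guide; if any have been held, the report should say which version each used.

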### Ethical and research and development approval

A favourable ethical opinion was obtained from NRES Committee for North of Scotland on 8th April 2013 (REC ref 13/NF/0018). NHS Highland and NHS Grampian R&D Management Approval was obtained on 9 April 2013 and 14 September 2013, respectively.

### Sample size

The nature of this study is a pilot RCT. Thus, a formal sample size calculation was not performed. The determined sample size of *n* = 40 was calculated based on the estimated number of participants expected to complete the 8-week program.

This number was achieved by the following calculation. Recommendation for pilot sample size calculation is 30 [56,57]. Literature suggest that attrition rate of approximately 25% is to be reasonably expected in mindfulness intervention studies [58]. A sample size of 40 with a 25% attrition rate will give an estimated sample of 30 subjects completing the 8-week program.

The approximate number of IBD patients is 600 in NHS Highland and 1,741 at NHS Grampian. With estimated recruitment rates of IBD interventional studies ranging between 10% and 20% (234 to 468 between the two sides), a sample size of 40 is reasonably achievable.

